## 1407 **9. STATISTICAL CONSIDERATIONS**

### 1408 **9.1 General Design Issues**

1409 This is a randomized control trial in which 100 adult participants with chronic low back pain (CLBP) will  
1410 be randomized to 6 weeks of twice a week sessions with verum acupuncture (VA) or placebo  
1411 acupuncture (PA). Participants and researchers will be blind to treatment assignment. Treatment  
1412 providers will not (and cannot) be masked to treatment assignment

1413 **Aim 1.** Explore the predictive relationship and the association between **ascending sensitization**  
1414 measures and clinical response to acupuncture.

1415 **Hypothesis 1:** augmented temporal summation (TS), and more wide-spread pain (WSP) (quantified by  
1416 number of painful areas marked by the participant on a standardized body map) will be associated with  
1417 greater pain reduction in the verum arm than in the placebo arm; decreased pressure pain threshold  
1418 (PPTr) will be associated with greater pain reduction in the placebo arm than the verum arm.

1419 **Aim 2.** Explore the predictive relationship and the association between **descending modulatory**  
1420 measures and clinical response to acupuncture.

1421 **Hypothesis 2:** decreased conditioned pain modulation (CPM), and more favorable psychological state,  
1422 measured by less pain catastrophizing, better self-efficacy in coping and in pain management, will be  
1423 associated with greater pain reduction in the verum than the placebo arm; expectation of positive  
1424 treatment outcome will be associated with pain reduction in both the verum and the placebo arm.

1425 **Aim 3. Exploratory model building** to predict pain reduction by electroacupuncture.

1426 **Hypothesis 3.** A mathematical model relating key baseline characteristics to percent pain reduction will  
1427 be developed using advanced techniques, and this model will be tested using cross-validation within the  
1428 proposed pilot.

1429

### 1430 **9.2 Sample Size and Randomization**

#### 1431 **Participants**

1432 The project will enroll 100 adults (ages 21-65 years) who meet criteria for chronic axial low back pain  
1433 without radicular symptoms. Participants with CLBP will be randomly assigned to an equal duration of  
1434 acupuncture treatment or placebo.

#### 1435 *Power Analysis*

1436 The objectives of aim 1 are to 1) explore the predictive relationship between ascending factors of  
1437 interest and pain reduction due to our interventions; 2) test the association between the ascending  
1438 factors and pain reduction. However, because the former is exploratory in nature, we will design our  
1439 study to power for the latter objective. Specifically, we compute the number of patients needed to find  
1440 an association between key baseline parameters (pressure pain threshold, temporal summation (TS), or  
1441 widespread pain) and pain reduction due to verum treatment. With 50 patients per arm, we will be able  
1442 to detect a moderate correlation of 0.4 (supported by literature for pressure pain threshold and TS)  
1443 with approximately 80% power with alpha of 0.05 using Fisher's transformation. Next, to determine if  
1444 the association is stronger in the verum than the sham arm, we will test the interaction between  
1445 treatment and the baseline parameters. Fifty patients per arm will provide 80% power (with alpha of  
1446 0.05) to detect a moderate difference of 0.5 between correlation from the verum arm and that from the  
1447 sham arm. Therefore, we are adequately powered to detect a moderate association between baseline  
1448 parameters and the clinical response in the verum acupuncture arm and a moderate difference in the  
1449 strengths of these associations between the verum and the sham treatment group.

1450 Similar calculation with identical numbers can be found for aim 2 (descending factors). Note prior  
1451 literature supports a moderate association around 0.4 between catastrophizing and pain reduction as  
1452 well as between self-efficacy and pain reduction in patients suffering from chronic low back pain.

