### **Sample Size and Population**

This project will recruit men and women with axial chronic lower back pain (greater than 3 months) and no radicular symptoms. Participants must be within the age range of 21 to 65. A total of 100 participants will be enrolled in the project.

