#### 1100 *Eligibility Determination and Enrollment*

1101 *Eligibility determination:* The patient will undergo the evaluations above and the research team will  
1102 check the patient's eligibility against an inclusion/exclusion checklist. Once the patient passes the  
1103 checklist, he/she will be deemed eligible for the study and will be enrolled (see below). If the patient is

1104 not eligible, we will ask his/her permission to be included in the database so we can contact him/her for  
1105 future studies which may be suitable.  
1106 **Enrollment procedure:** Once the patient is deemed eligible, he/she will be enrolled for the project and  
1107 assigned a project ID. The enrollment date will be the date of the screening visit and will be recorded in  
1108 the SNAPL Central Database. Enrollment date and future visit dates will also be recorded in the project  
1109 database on REDCAP for tracking purposes.

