#### 1453 *Randomization*

1454 When a new participant has passed the initial screening and baseline visit, he/she will be randomized to  
1455 receiving either VA or PA with equal chance. An R program for variable block randomization will be used.  
1456 We will randomize patients in blocks with block sizes randomly selected from 6, 8 and 10. Our lab  
1457 manager or his associates (who are NOT immediately related to the proposed project) will run the  
1458 randomization program and inform the treatment assignments to each provider via secure emails. Note  
1459 that the participant will be able to pick the acupuncturist based on ease of access (commute time).

1460 Details of Blinding can be found in Section 6.2.3 Blinding. Details on randomization can be found in  
1461 Section 4.3.2.

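### The 80% power stated for the verum-versus-sham interaction rests on unstated correlations and sidedness; two-sided, a difference of 0.5 gives about 72% at the 0.4 that section 9.2 cites

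*Protocol*

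**What the plan says.** The power paragraph in protocol section 9.2 makes two calculations.

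- **Single arm.** "With 50 patients per arm, we will be able" "to detect a moderate correlation of 0.4" in the verum arm, "with approximately 80% power with alpha of 0.05 using" Fisher's transformation. The value of 0.4 is attributed to literature on pressure pain threshold and temporal summation.
- **Interaction.** "Fifty patients per arm will provide 80% power (with alpha of" 0.05) "to detect a moderate difference of 0.5 between correlation from the verum arm and that from the" sham arm.

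The paragraph then calls the trial adequately powered for both. It carries the same numbers over to Aim 2, where it again cites associations of around 0.4 (catastrophizing, self-efficacy). It does not give the two correlations behind the 0.5, or say whether either test is one-sided or two-sided.

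Section 9.6 bases its association tests on 95% confidence intervals. In its worked example, temporal summation, it expects the sham association to be close to null.

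**The concern.** The sampling error of a correlation depends on its size, so a difference of 0.5 does not fix the power: 0.25 vs -0.25 and 0.6 vs 0.1 are the same difference with different power. A single figure of 80% therefore cannot be checked from the stated inputs, and the most natural inputs give less.

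Most of Hypotheses 1 and 2 are claims that an association is stronger in one arm than in the other, and the interaction is the test of those claims. If it turns out non-significant, a reader who relies on section 9.2 will take it as the result of an adequately powered test and may conclude that the predictors do not act differently under verum and sham. With power nearer 70%, or nearer 50% for the smaller contrast, that conclusion would not be justified.

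**Working it through.** **Inputs.** From section 9.2: 50 per arm, alpha 0.05, single-arm correlation 0.4, difference 0.5, Fisher's transformation (named for the single-arm figure). From the Randomization text of section 9.2: allocation to "receiving either VA or PA with equal chance". From section 9.6: 95% intervals, and a near-null sham association for temporal summation. Sidedness and the two arm correlations are not given, so they are varied.

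**Formulas.** Single arm: power = Φ(atanh(r)·√(n-3) - z). Two arms: power = Φ(|atanh(r1) - atanh(r2)| / √(2/(n-3)) - z). Here z = 1.96 two-sided or 1.645 one-sided. With n = 50, √47 = 6.856 and √(2/47) = 0.2063.

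**Step 1: the plan's single-arm figure.** atanh(0.4) = 0.4236, and 0.4236 × 6.856 = 2.90. Two-sided: Φ(2.90 - 1.96) = 82.8%. One-sided: 89.6%. The plan says approximately 80%, which fits the two-sided test and not the one-sided one.

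**Step 2: the interaction, difference 0.5.**

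| Verum vs sham | Standardised difference | Two-sided 0.05 | One-sided 0.05 |
|---|---|---|---|
| 0.25 vs -0.25 | 0.5108/0.2063 = 2.48 | 69.7% | 79.7% |
| 0.4 vs -0.1 | 0.5240/0.2063 = 2.54 | 71.9% | 81.5% |
| 0.5 vs 0 | 0.5493/0.2063 = 2.66 | 75.9% | 84.6% |
| 0.57 vs 0.07 | 0.5774/0.2063 = 2.80 | 79.9% | 87.6% |
| 0.6 vs 0.1 | 0.5928/0.2063 = 2.87 | 82.0% | 89.0% |

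Solving for exactly 80% two-sided gives a verum correlation of 0.571 (sham 0.071).

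**Step 3: the temporal summation contrast.** Verum 0.4 against sham 0 is a difference of 0.4, not 0.5. 0.4236/0.2063 = 2.05, so power is 53.7% two-sided and 65.9% one-sided.

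**Step 4: what is detectable at 80%, two-sided.** The required gap on the z scale is (1.96 + 0.8416) × 0.2063 = 0.578. From 0.40 this leads to a sham correlation of about -0.15, a difference of about 0.55. From a sham correlation of 0 it requires a verum correlation of about 0.52.

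**Cross-check.** Section 9.2 speaks of testing the treatment-by-predictor interaction. Simulating a regression interaction t-test (20,000 runs, equal outcome SD in both arms, two-sided 0.05) gave 71.0% for 0.4 vs -0.1 and 52.5% for 0.4 vs 0, so the choice of test does not change the picture.

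**The case against.** **The 80% can be reproduced.** The sidedness is unstated and the sentence is worded directionally (stronger in verum than in sham). A one-sided 5% test at 0.4 vs -0.1 gives 81.5%. A two-sided test gives about 80% at 0.57 vs 0.07. The 0.4 belongs to the single-arm calculation and is not stated as the verum value behind the 0.5. Section 2.2 even quotes a correlation of 0.628, for conditioned pain modulation and duloxetine response in diabetic neuropathy. All of this stands, so the figure cannot be called an outright arithmetic error. But the one-sided reading requires a change of sidedness between adjacent calculations at the same stated alpha, and no one-sided test is declared anywhere. Section 9.2 does not invoke the 0.628, which concerns another treatment and condition, and itself cites 0.4 for both aims.

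**The test is secondary and exploratory.** Section 9.6 makes prediction error the primary analysis and association the secondary one, and defers confirmation to larger trials. That lowers the weight of the point. It does not remove it, because section 9.2 chooses to power the trial on association and states a conclusion about power for the interaction.

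**A null sham association is not the general hypothesis.** This is correct. It is stated for temporal summation as the worked example. Pressure pain threshold is hypothesised to act more under placebo, and expectation in both arms.

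**Loss of participants.** A reader might infer a further shortfall, since "A total of 100 participants will be enrolled in the project" and "The enrollment date will be the date of the screening visit". The documents do not establish one. The Précis (Design and Outcomes), section 3 and section 9.1 say that 100 will be randomised. Section 5.4.5 collects post-treatment data on non-completers, and section 6.2.6 derives the primary outcome from daily scores after early termination.

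**Conclusion.** The stated 80%, and the conclusion of adequate power for the interaction, are not supported as written. On a two-sided 5% test with 50 evaluable per arm, a difference of 0.5 has about 72% power at the cited verum correlation of 0.4, and 70% to 76% across the pairs from 0.25 vs -0.25 to 0.5 vs 0. It reaches 80% only from a verum correlation of about 0.57 upwards. This rests on the two-sided reading, which is an inference from the single-arm figure and the 95% intervals, and on taking 0.4 as the verum value.

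The temporal summation contrast of 0.4 vs 0 is a separate matter. There the claim of adequate power fails under either sidedness (54% or 66%).

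Two stronger statements might be inferred and should not be. The first is that the design cannot give 80% for a difference of 0.5: it can, under assumptions that the protocol does not exclude. The second is that 54% is the power delivered for the stated difference: it belongs to a difference of 0.4, and a null sham correlation with the stated 0.5 gives 76%.

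**What to change.** In section 9.2:

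1. State the verum and sham correlations behind the interaction calculation, and the sidedness of the test.
2. If the test is two-sided, restate the power with 50 evaluable per arm as about 72% for 0.4 vs -0.1, 76% for 0.5 vs 0 and 54% for 0.4 vs 0. Give the difference detectable with 80% power as about 0.55 (0.40 vs -0.15) or 0.52 (0.52 vs 0).
3. Remove the claim of adequate power for the interaction, and say that it will be reported as an estimate with a 95% confidence interval. Section 9.6 already plans to estimate it.
4. Apply the same wording to Aim 2, which borrows the same numbers.

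The single-arm statement can stay. The cost is protocol wording and a less favourable stated figure; sample size, conduct and data collection do not change.

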#### 1453 *Randomization*

1454 When a new participant has passed the initial screening and baseline visit, he/she will be randomized to  
1455 receiving either VA or PA with equal chance. An R program for variable block randomization will be used.  
1456 We will randomize patients in blocks with block sizes randomly selected from 6, 8 and 10. Our lab  
1457 manager or his associates (who are NOT immediately related to the proposed project) will run the  
1458 randomization program and inform the treatment assignments to each provider via secure emails. Note  
1459 that the participant will be able to pick the acupuncturist based on ease of access (commute time).

1460 Details of Blinding can be found in Section 6.2.3 Blinding. Details on randomization can be found in  
1461 Section 4.3.2.

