#### 4.3.2 Randomization

When a new participant has passed the initial screening and baseline visit, he/she will be randomized to receiving either VA or PA with equal chance. An R program for randomization will be used. We will randomize patients within each of the 7 acupuncture sites with equal chance of receiving either VA or PA. Our lab manager or his associates (who are NOT immediately related to the proposed project) will run the randomization program and inform the treatment assignments to each provider via secure emails. Note that the participant will be able to pick the acupuncturist based on ease of access (commute time). Lastly, block randomization will be employed within each of the 7 acupuncturists to minimize chance imbalance in the number of verum vs sham assignments for each provider in case there is a large difference in the number of patients assigned to a provider (we observed this situation in the current P01 trial).

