#### Randomization

Randomization to a specific treatment arm will take place after the baseline visit, before the first treatment session. The study intervention will begin as soon as possible (within 1 week ideally) after the Baseline Visit. The randomization procedure is detailed below:

- ☐ Participant becomes ready for treatment after completion of baseline visit
- ☐ Research team assign participant to an acupuncturist based on participant's location preference.
- ☐ Research team provide participant the acupuncturist's contact info and the acupuncturist participant's contact info.
- ☐ Acupuncturist and participant reach out to each other and schedule first treatment appointment.
- ☐ Once the appointment is made, acupuncturist alert research team, who then alert an outside party (another RC from or lab not related to our project) who then performs randomization by entering the participant ID and acupuncturist ID into the randomization program.
- ☐ The randomization program is written in R, and we will stratify randomization per acupuncturist with a block of 4 within each acupuncturist, to ensure balanced treatment assignment within each provider.
- ☐ The unrelated RC will then securely email the treatment assignment (participant ID and treatment arm) to the acupuncturist.

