## 9.6 Data Analyses

**Aim 1. Explore the predictive relationship and the association between ascending sensitization measures and clinical response to acupuncture.**

**Planned analysis:** There are two specific goals of the analysis: (1) explore the predictive relationship between key baseline parameters and treatment response (pain reduction) accordingly by arm; and (2) examine the associations between baseline predictors and treatment response by arm. The identified association can help us understand the underlying mechanism of the treatment effect from acupuncture and, AND assist in building good subsequent prediction models. To this end, taking temporal summation (TS) first as an example, we will first estimate the correlation coefficients between baseline TS and the primary outcome (% pain reduction immediately after treatment) and then perform multivariate linear regression with clinical pain reduction as the continuous dependent variable and TS and potential confounding factors such as the demographic variables and the baseline pain level as independent variables in the verum arm. We will estimate the regression coefficients and their 95% confidence intervals, which will be used to formally test association between TS and pain reduction with or without adjustment of potential confounders. To evaluate the predictiveness of TS (with other patients' characteristics) to pain reduction, we will also calculate the mean squared prediction error of the multivariate regression model. Variable selection method such as lasso may be used to remove unnecessary predictors from the model and cross-validation will be used to estimate the prediction accuracy to account for the adaptive model building step. Likewise, we will repeat the analysis in the sham arm. Specifically, we will test the presence of the association by examining if zero is inside the interval for confirming the hypothesis that the association is close to null in the sham arm. We will also estimate the interaction between the treatment group and TS to determine if decreased TS better predicts treatment response to verum than to sham acupuncture. Note that factors which are equally predictive to the pain reduction in both arm in general do not have interaction with the treatment.

1514 In summary, the primary objective will be to assess the predictiveness of baseline TS to pain reduction;  
1515 and the primary outcome of pain reduction will be the difference in pain between baseline and  

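### Section 9.2 (variable blocks of 6, 8 and 10) contradicts Section 6.2.2 (fixed block of 4 within each acupuncturist), and Section 4.3.2, to which 9.2 refers, gives no block size

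*Protocol*

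**What the plan says.** Three sections of the current protocol describe how participants are allocated.

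- Section 9.2 (Randomization): "An R program for variable block randomization will be used", followed by "We will randomize patients in blocks with block sizes randomly selected from 6, 8 and 10". No stratum is named. The section closes with "Details on randomization can be found in" Section 4.3.2.
- Section 4.3.2: "block randomization will be employed within each of the 7 acupuncturists". No block size is given.
- Section 6.2.2 (Randomization): "we will stratify randomization per acupuncturist with a block of 4 within each acupuncturist".

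Section 6.2.2 also sets the order of events. The baseline visit is completed, the participant is matched to an acupuncturist by location, and the two arrange the first session. Then: "Once the appointment is made, acupuncturist alert research team". An RC from outside the project runs the program and emails the assignment to the acupuncturist. Section 6.2.3 leaves the acupuncturists unblinded and makes the PI and research assistant the assessors.

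For the analysis, the Aim 1 regression in Section 9.6 includes "potential confounding factors such as the demographic variables and the baseline pain level as independent variables". Acupuncturist and site are not named anywhere in Section 9.6, including the treatment-by-TS interaction and the verum-sham comparison in the selected subgroup under Aim 3.

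**The concern.** The allocation rule is part of the design, and a reader must be able to tell what was run. Here the statistical section and the procedural section give different block sizes, one fixed and one variable.

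The choice has consequences. Small fixed blocks within provider hold balance tightly but are easy to predict, and the people who see each stratum's assignments are the unblinded acupuncturists. Section 12.1 counts the acupuncturists as part of the research team, and Section 10.3.1 gives team members a copy of the protocol, which prints the block of 4. The assessors are exposed too: Section 6.2.5 has the PI or RC unblind each participant at the post-treatment visit. If they know the block size, assignments already disclosed for one provider can reveal that of a later participant in the same block whose outcome is still to be assessed.

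A second, smaller matter is that the trial stratifies on acupuncturist, and participants choose the provider by ease of travel. Provider is therefore not randomised with respect to the baseline predictors, yet no model names it.

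**Working it through.** **1. Can one program satisfy both sections?** Section 6.2.2 allows the size {4}, fixed. Section 9.2 allows {6, 8, 10}, drawn at random. The sets share no value, so the answer is no. The only cross-reference leads to Section 4.3.2, which names the stratum but no size. The revision history for version 3.0 records the move to blocks of 4 stratified by acupuncturist, which suggests that 9.2 was left behind. This is an inference: the log calls the superseded scheme simple randomisation and does not mention 6, 8 and 10.

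**2. How predictable is each size?** In a permuted block of size 2k with equal allocation, the expected share of assignments fully determined by the earlier ones is 1/(k+1). For size 4, the patterns starting with A are AABB (2 determined), ABAB (1) and ABBA (1). Their mean is 4/3, and (4/3)/4 = 1/3. The best-guess rate for size 4 is (1/2 + 2/3 + 2/3 + 1)/4 = 70.8%.

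| Block size (known) | Certain in advance | Best-guess rate |
|---|---|---|
| 4 | 33% | 70.8% |
| 6 | 25% | 68.3% |
| 8 | 20% | 66.6% |
| 10 | 17% | 65.3% |

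**3. What does the choice do to balance?** This is a simulation with 4,000 runs, 100 participants and 7 acupuncturists (the number in the Précis and Section 4.3.2). The split by acupuncturist is an assumption: equal (14 or 15 each), or one main provider (52, with 8 for each of the other six). Imbalance is the absolute difference between arm counts within an acupuncturist.

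| Scheme | Chance that some acupuncturist is imbalanced by 4 or more: equal / 52 + 6×8 | Assignments certain in advance (sizes known) |
|---|---|---|
| Blocks of 4 within acupuncturist | 0% / 0% | 29-33% |
| 6/8/10 within acupuncturist | 7% / 1% | 15-16% |
| 6/8/10 without strata | 94% / 91% | 19% |

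The 15-16% and 19% assume that each randomly drawn block size is also known, so they are upper bounds. The last row only shows what is at stake in the stratum; it does not assert that 9.2 means this.

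**4. What would adding acupuncturist cost?** Section 9.2 states approximately 80% power for a correlation of 0.4 with 50 per arm and alpha 0.05, using Fisher's transformation. Two-sided, with k adjusted covariates, power = Φ(atanh(r)·√(n − 3 − k) − 1.96).

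- k = 0: 0.4236 × √47 − 1.96 = 0.944, power 82.8%. The protocol's figure is met, slightly on the safe side; n = 47 gives 80.2%.
- k = 6 (seven acupuncturists as indicators), partial r still 0.4: 0.4236 × √41 − 1.96 = 0.753, power 77.4%. The n per arm for 80% rises from 47 to 53.
- If acupuncturist explains part of the outcome variance and is unrelated to the predictor, partial r = 0.4/√(1 − ICC). For assumed ICCs of 0.02, 0.05 and 0.10, power is 78.3%, 79.7% and 82.1%. The documents give no ICC.

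**The case against.** The strongest reply is that this is one un-updated paragraph. Section 6.2.2 sets out the procedure step by step, the version 3.0 log agrees with it, and the sample size is untouched. That explains the conflict but does not remove it: 9.2 is current text in the statistical section.

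Three stronger readings are tempting and should not be drawn.

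- *That 9.2 prescribes unstratified randomisation.* It only names no stratum, and it refers to a section that stratifies. The block-size conflict is certain; a conflict over strata is inferred from silence.
- *That the block of 4 opens the trial to serious selection bias.* The research team determines eligibility and enrols at screening, baseline measures are complete, and the provider is chosen, all before randomisation. What remains is the order of first appointments among participants already enrolled and waiting for the same acupuncturist, plus guessing by assessors. With sizes known, the guess rate for a block of 4 is only 2.5 to 5.5 points above that for 6, 8 or 10. Larger variable blocks also loosen balance within provider, which is the aim stated in 4.3.2.
- *That the plan excludes acupuncturist from the models.* The covariates in 9.6 are given as examples, and an analysis plan not seen here may add it. Omission from an open list is not an error in itself.

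The objection to adjustment also stands in part: six fixed effects within one arm would gain no power across the ICC range shown.

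**Conclusion.** The contradiction in block size holds as written and needs no assumption. Sections 6.2.2 and 9.2 cannot both describe the allocation, and 4.3.2 does not decide between them. That 9.2 is the outdated text is probable, not certain.

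Predictability is a real but limited weakness of a known block of 4. About one third of assignments are certain in advance, provided that the size and the earlier assignments in the stratum are known.

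Naming acupuncturist in the models is a secondary improvement, justified because the trial stratifies on it and participants choose their provider. No figure for lost precision is claimed, since it would rest on an ICC that the documents do not supply.

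**What to change.** 1. State in Sections 4.3.2, 6.2.2 and 9.2 the one scheme actually programmed, stratified by acupuncturist, with fixed or varying blocks as run. If the program changed during the trial, record when. Confirm the number of strata at the same time: 4.3.2 has seven acupuncturists, while 5.4.1 describes a main acupuncturist plus one in each of three areas. The cost is wording.
2. For any remaining participants, hold the block sizes in a restricted randomisation file kept by the outside randomiser, and leave them out of the copies given to acupuncturists and assessors. The cost is negligible. Changing to varying sizes is optional; with 6/8/10 within acupuncturist, the chance of an imbalance of 4 or more in some stratum goes from 0% to 7% under an equal split.
3. In 9.6, or in the analysis plan, include acupuncturist in the treatment-by-predictor interaction models and the verum-sham subgroup contrast, preferably as a random effect. Include it in the within-arm regressions as a sensitivity analysis only. The correlations can stay as planned. The downside is greatest for six fixed effects within one arm of 50, where power for r = 0.4 could fall from about 83% to 77% if acupuncturist explains no outcome variance. A random effect should cost less.
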